## Abstract

**Background:**

Diagnostic decision making, especially in emergency departments, is a highly complex cognitive process that involves uncertainty and susceptibility to errors. A combination of factors, including patient factors (eg, history, behaviors, complexity, and comorbidity), provider-care team factors (eg, cognitive load and information gathering and synthesis), and system factors (eg, health information technology, crowding, shift-based work, and interruptions) may contribute to diagnostic errors. Using electronic triggers to identify records of patients with certain patterns of care, such as escalation of care, has been useful to screen for diagnostic errors. Once errors are identified, sophisticated data analytics and machine learning techniques can be applied to existing electronic health record (EHR) data sets to shed light on potential risk factors influencing diagnostic decision making.

**Objective:**

This study aims to identify variables associated with diagnostic errors in emergency departments using large-scale EHR data and machine learning techniques.

**Methods:**

This study plans to use trigger algorithms within EHR data repositories to generate a large data set of records that are labeled *trigger-positive* or *trigger-negative,* depending on whether they meet certain criteria. Samples from both data sets will be validated using medical record reviews, upon which we expect to find a higher number of diagnostic safety events in the trigger-positive subset. Machine learning will be used to evaluate relationships between certain patient factors, provider-care team factors, and system-level risk factors and diagnostic safety signals in the statistically matched groups of trigger-positive and trigger-negative charts.

**Results:**

This federally funded study was approved by the institutional review board of 2 academic medical centers with affiliated community hospitals. Trigger queries are being developed at both organizations, and sample cohorts will be labeled using the triggers. Machine learning techniques such as association rule mining, chi-square automated interaction detection, and classification and regression trees will be used to discover important variables that could be incorporated within future clinical decision support systems to help identify and reduce risks that contribute to diagnostic errors.

**Conclusions:**

The use of large EHR data sets and machine learning to investigate risk factors (related to the patient, provider-care team, and system-level) in the diagnostic process may help create future mechanisms for monitoring diagnostic safety.

**International Registered Report Identifier (IRRID):**

DERR1-10.2196/24642

## Introduction

### Background

Diagnostic decision making is a complex cognitive process involving uncertainty and susceptibility to errors. According to the National Academies of Science, Engineering, and Medicine, diagnostic error is defined as the “failure to establish an accurate and timely explanation of the patient’s health problem(s) or communicate that explanation to the patient” [1]. Approximately 30% of malpractice claims and more than 8% of adverse events in medicine are related to diagnostic errors [2], yet most are never reported [3]. Other researchers reported a 15% rate of diagnostic error in clinical medicine [2], with 5% of adults misdiagnosed annually in outpatient care [1,4] and about 15%-30% in the context of the emergency departments (EDs) [5].

The ED, in particular, is known as a *natural laboratory for the study of errors* [3], with a high prevalence of diagnostic errors [3]. Time-pressured decision making in a high-paced, high-volume, and chaotic ED environment increases the risk of erroneous diagnostic decisions [6]. Diagnostic errors are one of the most common types of errors in the ED [3]. Although precise error rates are lacking, they involve 65% of all closed malpractice claims [7]. A conservative estimate suggests that 1 out of every 10 diagnoses is subject to some level of error, and half of the errors cause harm or escalation of the health condition [1,8-10]. This results in approximately 7 million harmful errors out of the 139 million annual ED visits in the United States, making diagnostic safety a high priority for ED-related research [11].

Errors occurring in the ED often have multifactorial origins [12], and little is known about these factors [13]. In the absence of a unified taxonomy for contributing factors [14,15], the National Academies of Science, Engineering, and Medicine report [1] *Improving Diagnosis in Health Care* highlighted that the diagnostic process is not limited to the patient-provider interaction, and errors may result from the complex interplay of parameters related to patients (eg, health literacy, presenting symptoms, complexity, and behaviors), provider-care teams (eg, the cognitive load on providers and information gathering and synthesis), and systems (eg, health information technology, crowding, and interruptions).

There is an urgent need to design, implement, and develop novel methods to identify and reduce the risks related to the diagnostic process in complex ED microsystems. These methods should account for the dynamics of human-system interaction during the diagnostic process and address the inherent risks involved in these interactions. Efficiently screening large and ever-growing data sets, such as electronic health records (EHRs), can help identify cases with diagnostic errors and associated risk factors for mitigation strategies [16]. Data mining can be used to identify these factors and study their influence on diagnostic errors.

Data mining is a knowledge discovery method [17] that encompasses various algorithms to identify patterns and trends in large-scale data sets [18,19], such as EHRs. Previous research has shown the application of data mining techniques in the extraction of useful knowledge from large data sets in the fields of medicine and biology [20]. These algorithms use data to help scientists find input variables that have a significant relationship with the output variable. Most advancements in this type of analysis are achieved by incorporating techniques such as association rule mining (ARM), classification and regression trees (CART), and chi-square automated interaction detection (CHAID). ARM aims to extract frequent patterns, meaningful correlations, or causal structures within a data set [21] that satisfy the predefined minimum support and confidence from a given database [18]. This technique has been used in detecting disease co-occurrence, discovering adverse drug reactions, identifying risk factors for heart disease, and surveilling public health [22]. In contrast, decision trees are known to be effective in a variety of domains, with CART and CHAID being the two most popular decision tree techniques [17]. They are used to model the relationship between predictor variables and the outcome variable by recursive partitioning of large heterogeneous data sets into two or more homogeneous nodes [23].

### Objective

This protocol describes the application of data mining and machine learning techniques to understand diagnosis-associated risks in the ED and improve diagnostic safety. It focuses only on aim 1.3 of the recent *Improving Diagnosis in Emergency and Acute Care–Learning Laboratory* (IDEA-LL) grant awarded by the Agency for Healthcare Research and Quality (Figure 1). IDEA-LL is an actionable and patient-centered program for diagnostic safety surveillance and intervention based on the available data in EHRs. Diagnostic safety events will be identified through a review of EHR *triggers* related to events that are known to be associated with errors in the diagnosis process. After validation using EHR data, data mining and machine learning techniques will be utilized to compare an at-risk, trigger-positive sample with trigger-negative charts. This specific part of the grant will provide evidence-based guidance to identify factors with the highest prevalence among the trigger-positive cases and information that will be used in future projects (aim 2) to identify causal relationships and inform the design of decision support systems.

**Figure 1 figure1:**
[figure not shown]
The 3 aims of the Agency for Healthcare Research and Quality-funded Improving Diagnosis in Emergency and Acute Care–Learning Laboratory project and the detailed steps of this study specifically focusing on aim 1.3 to identify patient-, provider-care team–, and system-level–factors affecting the risk for diagnostic error. ED: emergency department; EHR: electronic health record.

## Methods

### Setting

#### Population and Site Participation

Patient encounters from 4 EDs will be used in this study, including 2 from the Mayo Clinic system and 2 from the University of Michigan Health System. The institutional review boards from participating institutions approved the study protocol (19-009115, HUM00173662, 1696020-1). In this study, we will extract clinical data as part of data mining using triggers and compare them with nontriggered charts through the EHR systems at 4 EDs. Diversity of racial and ethnic backgrounds is represented in the 4 EDs by including all ages, races, ethnicities, and genders.

#### Sample Size Justifications and Power Calculation

We will estimate the sample size based on a power analysis with a two-tailed α=.05 and power of 85% for a predefined number of 10 independent variables that predict the diagnostic error yes or no outcome.

#### Sampling for Control

The control includes visits that do not meet the criteria for any trigger. We will include all ED visits in the two health systems for the entire study period (July 1, 2017-December 31, 2019). For each trigger-positive case, we will match a single trigger-negative encounter based on the availability of cases through a hierarchical procedure, which matches the encounters based on age group, gender, provider, the reason for visit, and the arrival date and time. This one-to-one matching of trigger-positive and trigger-negative cases will also help to eliminate the imbalance classes. To accommodate the potential heterogeneity across sites, the measurements will be reported as site-specific quartiles [24]. For patients with multiple ED or hospital visits during the study period, each record will be considered separately.

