### Conduct of the Study

#### Overview

This study aims to identify the factors that may interfere with the diagnostic process in the ED that potentially lead to missed, delayed, or incorrect diagnoses. On the basis of our previous work, we will use a series of electronic triggers (triggers) to identify ED encounters with potential diagnostic errors from the EHR database. Each trigger has a predefined set of inclusion and exclusion criteria implemented in Structured Query Language (SQL) and configured for specifications of each site in the study. Each site currently uses an Epic EHR system with minimal variations owing to its specific needs. These differences will be identified and accounted for after the focus interviews with the providers. The Epic specialists at both sites are in constant communication with the research team to apply the most accurate mapping of the factors and parameters between the 2 sites. The protocol is thought to be generalizable to other EHR systems, as we emphasize the analysis of common ED concepts rather than database variables specific to Epic. All SQL queries can be modified to match other systems (eg, Cerner) by matching concepts and keywords. Table 1 provides an initial list of 6 EHR-based triggers proposed in IDEA-LL after reviewing the literature on current triggers, surveying medical directors, and using a Delphi consensus process [32]. We will start our study with the first 3 triggers, including the unscheduled visit within 10 days resulting in admission, care escalation to intensive care unit within 24 hours, or death in the ED or within 24 hours of ED departure time. If for any reason, one or more of the triggers do not perform well, the triggers from the backup set will be used.

**Table 1 table1:** Proposed electronic trigger algorithms for identifying diagnostic errors.

Trigger algorithm			Description

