**Initial set of triggers**			
	Trigger 1: unscheduled return	Unscheduled return visit with admission within 7 to 10 days from the index ED^a^ visit.	
	Trigger 2: care escalation	Care escalation from the inpatient unit to the ICU^b^ within 6, 12, or 24 hours with ED attribution.	
	Trigger 3: death	All deaths in the ED or within 24 hours of admission—exclusive of palliative care.	

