#### Step 1: Sampling of Trigger-Positive and Trigger-Negative Charts

This step will apply the EHR-based trigger algorithms (Table 1) to the EHR data repositories that include ED encounters at the 2 sites, creating large data sets of statistically matched groups (for demographics and medical comorbidity or severity) for trigger-positive and trigger-negative (control) charts [36]. The inclusion and exclusion criteria for individual triggers will be refined after an iterative review of random samples of charts. We anticipate using 3 triggers that have the best predictive value for diagnostic errors.

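### Controls for every trigger come from one pool of non-triggered visits, so Trigger 2 cases can be matched to discharged visits that could never have been positive, and Step 4 can return eligibility as risk

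*Protocol article*

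**What the plan says.** The protocol article, Sampling for Control, sets the rule for controls: "The control includes visits that do not meet the criteria for any trigger". The source is equally broad: "We will include all ED visits in the two health systems for the entire study period". Matching is one to one: "For each trigger-positive case, we will match a single trigger-negative encounter based on the availability of cases". It uses a hierarchical procedure that "matches the encounters based on age group, gender, provider, the reason for visit, and the arrival date and time".

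Step 1 describes the matching differently, as "statistically matched groups (for demographics and medical comorbidity or severity". Neither list contains ED or hospital disposition.

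The triggers have their own populations. Table 1 defines Trigger 2 as "Care escalation from the inpatient unit to the ICU" within a set number of hours, Trigger 1 as an unscheduled return with admission, and Trigger 3 as death, "exclusive of palliative care". The Overview under Conduct of the Study adds: "Each trigger has a predefined set of inclusion and exclusion criteria". The article does not say that these criteria also govern who may be a control.

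Step 4 takes the trigger label as the dependent measure. The CHAID paragraph treats a larger chi-square as the better split. The candidate predictors in Textbox 2 include hospital admission diagnosis, ED length of stay and number of lab tests for all triggers. For Trigger 2 they also include hospital disposition, next unit, ICU unit and time to ICU.

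**The concern.** A case-control comparison is informative when the controls come from the population that could have produced the cases. Here the analysis is organised by trigger, but the control pool is not. For Trigger 2 the risk set is patients admitted to a non-ICU inpatient unit. The pool also holds discharged patients, who have no inpatient stay from which to be escalated. For Trigger 1 the risk set is visits after which the patient could return. The pool also holds patients who stayed in hospital throughout the return window, and deaths that do not meet Trigger 3.

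ARM, CART and CHAID all look for the variables that best separate the labels. If cases are all admitted by definition and controls are not, admission and anything closely tied to it will separate them. The stated purpose of this aim is to supply risk factors for later causal work and decision support. Determinants of admission could be passed on as determinants of diagnostic risk.

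**Working it through.** **Inputs from the article.** One control pool, meeting no trigger, from all ED visits (Sampling for Control). Ratio 1:1 (same section). Disposition absent from both matching lists (Sampling for Control; Step 1). All Trigger 2 cases admitted (Table 1). Dependent measure is the trigger label (Step 4, CHAID).

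**Input not in the article.** The share *a* of matched Trigger 2 controls who were admitted. I assume 15% to 60%. The article has no figure of its own to reproduce here: its sample-size section gives alpha, power and 10 predictors, but no number of records.

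**One split on admission.** Label a record positive if admitted. All cases are classified correctly, and so are the 1 − *a* of controls who were not admitted. With equal groups,

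proportion correct = [1 + (1 − *a*)] / 2 = 1 − *a*/2.

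| Assumed share of controls admitted | Controls that could not have been positive (at least) | Records classified correctly |
|---|---|---|
| 15% | 85% | 92.5% |
| 25% | 75% | 87.5% |
| 40% | 60% | 80% |
| 60% | 40% | 70% |

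The second column is a minimum because a direct ICU admission from the ED is admitted but cannot be escalated from an inpatient unit. The corresponding Pearson chi-square is 2*n*(1 − *a*)/(1 + *a*) for *n* pairs. With an assumed *n* = 500 this is 739, 600, 429 and 250. These values scale with *n*, so the proportions are the more useful figures. If controls are limited to admitted visits, the indicator is constant and cannot split the groups.

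**Does it spread to other variables?** A null simulation used 1,000,000 visits. Severity was standard normal and drove admission through a logistic model (slopes 0.5 to 1.5). Admission shares were 15%, 25% and 40%. Trigger 2 occurred in 2% of admitted visits regardless of severity. All of these are assumptions, and nothing was matched. With controls from all trigger-negative visits, the AUC for severity was 0.58 to 0.78, although severity had no effect on escalation. With admitted controls only, it was 0.49 to 0.50. This shows the mechanism and that eligible controls remove it. It does not estimate the bias under the planned matching.

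**Which listed predictors are exposed?**
- Hospital admission diagnosis, hospital disposition and next unit exist only for, or differ by definition with, an inpatient stay.
- ICU unit and time to ICU are part of the Trigger 2 definition and would separate the groups even with admitted controls.
- Number of lab tests and ED length of stay may act as proxies for admission, depending on how close the matching is.

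**The case against.** The strongest reply is that the matching already deals with much of this. Step 1 plans matching on comorbidity or severity, and the other list includes age group, reason for visit and arrival time. All of these would probably raise the share of admitted controls and narrow the severity gap. Step 4 is also exploratory, with causal work deferred to another aim. Part of this stands: the gap is likely to be smaller than without matching, and its size is unknown. But the two matching descriptions differ, only one mentions severity, and neither fixes disposition. A discharged control remains possible under both.

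Several stronger readings are tempting, and the article does not support them.

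- *Step 4 will simply rediscover severity.* The severity matching in Step 1 rules out certainty here. What can be said is that the two matching sets disagree.
- *Age and boarding will appear as artefacts.* Age group is matched. Boarding is described under Qualitative Variables as a count of boarded patients in the system, and controls are matched on arrival date and time.
- *The Step 2 odds ratio is distorted.* Step 2 asks whether triggered charts contain more errors than non-triggered charts. For that screening question, all non-triggered visits are a legitimate comparator.
- *Palliative-care deaths contaminate the controls.* Read literally, such a death does not meet Trigger 3 and could enter the pool. The article does not say whether the exclusion only withholds the label or removes the visit, and the query criteria are not shown. This needs a clarifying sentence and is not an established error.
- *The analysis is not done by trigger.* Step 2 and the Results section already plan it by trigger. What is not trigger-specific is the control pool.

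**Conclusion.** The point holds for the Step 4 comparison, most clearly for Trigger 2 and in the same way for Trigger 1. The article states a control rule that admits visits outside the trigger's risk set, and neither matching list repairs it. Followed as written, it lets admission-linked predictors separate cases from controls through eligibility. The control rule should be changed before Step 4 is run.

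The size cannot be derived from the article. The range of 92.5% to 70% correct from a single split rests on the assumed 15% to 60% of Trigger 2 controls admitted, on 1:1 matching, and on every case being admitted, which Table 1 implies. It measures how far admission alone would separate the groups, not the bias in any other factor.

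**What to change.** For the Step 4 comparison:

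1. Draw controls separately for each trigger from visits eligible for it. For Trigger 2, use visits admitted from the ED to a non-ICU inpatient unit and not escalated. For Trigger 1, use visits where the patient left the ED alive and was able to return.
2. Apply each trigger's exclusions, including palliative care for Trigger 3, to cases and controls alike, and say so.
3. Reconcile the matching sets in Sampling for Control and Step 1 into one list.
4. Remove from the candidate predictors any variable that is part of the trigger's own definition, such as ICU unit and time to ICU for Trigger 2.

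Step 2 may keep all non-triggered visits as comparator if the result is described as screening yield.

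The cost is a further condition in each control query, followed by re-matching. Disposition and next unit are already on the Trigger 2 predictor list, so the plan must obtain them for controls in any case. The downside is a smaller candidate control pool, which may make close matching on provider and arrival time harder.

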##### Chi-square Automated Interaction Detection

CHAID is a decision tree algorithm that determines splitting based on statistical tests and has been used to model the relationship between the predictor variables and the outcome variable in many medical applications, such as identifying factors influencing inpatient mortality [17]. In our study, CHAID will help answer the question “Which combination of factors leads to higher trigger-positive risk and therefore a higher relative risk of diagnostic error?” CHAID splits the target into two or more categories using an exploratory analysis of the relationship between a dependent factor and several predictor factors [39]. To see if splitting the sample based on these predictors leads to statistically significant discrimination in the dependent measure (trigger labels), various independent factors will be evaluated using the chi-square test [40]. Despite regression, CHAID is capable of illustrating variable clusters through an iterative process. Adjusted *P* value measures are used to determine the best value of the partition or the best split, and splitting on a larger chi-square statistic indicates a more significant partition.

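### Repeat visits are handled as separate records, with no bar on matching a case to the same patient's other visit and no allowance for within-patient correlation in the chi-square tests

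*Protocol article*

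**What the plan says.** Sampling for Control sets the rules that matter here.

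- Control eligibility: "The control includes visits that do not meet the criteria for any trigger".
- Source: "We will include all ED visits in the two health systems for the entire study period", that is, July 1, 2017 to December 31, 2019.
- Ratio: "For each trigger-positive case, we will match a single trigger-negative encounter".
- Matching: a hierarchical procedure that "matches the encounters based on age group, gender, provider, the reason for visit, and the arrival date and time". Step 1 also speaks of groups matched for demographics and for comorbidity or severity.
- Repeat patients: "For patients with multiple ED or hospital visits during the study period, each record will be considered separately".

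Table 1 defines Trigger 1 as "Unscheduled return visit with admission within 7 to 10 days from the index" ED visit. Textbox 2 lists fields from both the previous and the return visit as Trigger 1 factors. Neither place says which of the two encounters carries the positive label.

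On testing, the CHAID section says that "various independent factors will be evaluated using the chi-square test", with adjusted P values used to choose the split. Step 2 plans odds ratios and hypothesis tests on reviewed charts. The article mentions no limit on records per patient, no patient-level clustering and no exclusion of a case patient's other visits.

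**The concern.** Two separate problems follow from the rule on repeat patients.

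**Self-matching.** A Trigger 1 event exists only because one patient came twice within days. If only one of the two visits is labelled positive, the other is an eligible control unless it meets a trigger in its own right. It agrees with the case on gender and nearly always on age group, and probably on reason for visit and approximate date. Such a pair cannot show a difference on any fixed patient characteristic, so patient-level associations are diluted. In Step 2, a reviewer reading the control chart may meet the same episode's error in a record labelled trigger-negative, which blurs the comparison meant to validate the trigger.

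**Correlated records.** Patients who attend often can supply several records with the same label. An ordinary chi-square test counts each as new information. For factors that are stable within a patient, P values become too small, and a few frequent attenders can produce a split.

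What is at stake is the list of risk factors, the study's main product, which is meant to feed later causal work and decision support. False patient factors could enter it and true ones could be missed.

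**Working it through.** The article gives no sample size, effect size, visits per patient or within-patient correlation, so there is no figure of its own to reproduce. Everything below except the nominal 5% level (two-tailed α of .05 in the sample size section) is an assumption used to show scale.

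**1. Can a case be matched to the same patient's other visit?** There are three possible labellings of a Trigger 1 pair.
- Only the index visit is positive: the return visit is eligible unless it meets a trigger itself.
- Only the return visit is positive: the index visit is eligible on the same condition.
- Both are positive: this self-match is blocked, but two same-label records of one patient enter the data.

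The text does not say which applies. Each leaves one of the two problems open.

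**2. Correlated records: size of a nominal 5% test.** Let m be records per patient, and ρ the product of the within-patient correlations of factor and label.

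Design effect: DE = 1 + (m − 1)ρ. True size: 2[1 − Φ(1.96/√DE)].

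Assume m = 2 and both correlations between 0.2 and 0.5.
- Low end: ρ = 0.2 × 0.2 = 0.04, DE = 1.04, true size 0.055.
- High end: ρ = 0.5 × 0.5 = 0.25, DE = 1.25, true size 0.080.

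If the label (or the factor) is constant within a patient, its correlation is 1 and ρ equals the other correlation. With 0.2 to 0.5, DE is 1.2 to 1.5 and the true size 0.074 to 0.110.

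**3. Extreme case of correlated records.** Suppose 500 patients per group, factor and label both constant within patient, and a share s of patients contributing 3 records each. Then DE = (1 + 8s)/(1 + 2s), the sum of squared record counts over the sum of counts. The simulation used 4,000 runs, a factor with 30% prevalence and no true association.

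| s | DE | True size, formula | True size, simulated |
|---|---|---|---|
| 0 | 1.00 | 0.050 | 0.048 |
| 10% | 1.50 | 0.110 | 0.109 |
| 20% | 1.86 | 0.150 | 0.156 |
| 40% | 2.33 | 0.199 | 0.199 |

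**4. Self-pairs.** Let q be the share of 500 pairs in which the control is the case patient's own other visit. Take a patient factor with prevalence 30% in cases and 20% in true controls, so OR = (0.3/0.7)/(0.2/0.8) = 1.71. Control prevalence becomes 0.2(1 − q) + 0.3q. Under no association, the variance of the difference shrinks by the factor (1 − q), so the ordinary test has true size 2[1 − Φ(1.96/√(1 − q))].

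| q | Control prevalence | OR seen | True size, formula | True size, simulated |
|---|---|---|---|---|
| 5% | 20.5% | 1.66 | 0.044 | 0.051 |
| 10% | 21.0% | 1.61 | 0.039 | 0.036 |
| 25% | 22.5% | 1.48 | 0.024 | 0.023 |
| 50% | 25.0% | 1.29 | 0.006 | 0.005 |

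**5. Direction.** Same-label repeats make the test too liberal. Self-pairs make it too conservative and shrink the association. Nothing in the design makes them cancel.

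**The case against.** The best reply is that self-matching is not shown. Read plainly, Table 1 makes the return visit itself the trigger event, so it could not be a control. Textbox 2 fits a single positive record built from both visits. This removes one route only: if the return visit is the positive record, the index visit becomes the eligible control unless it too is labelled, and the article does not say that it is.

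The matching list also works against self-pairs. A return days later may be under another provider and at another hour, and the pool is every ED visit in two health systems over two and a half years. This stands. A reader might infer that every Trigger 1 case brings its own return visit as one of its closest controls; the documents do not support that.

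A reader might also infer that the plan assumes records to be independent. It does not say so. It says that records are considered separately, and the word independent in the CHAID section describes predictor variables. The assumption comes with the ordinary chi-square test, for which no clustered version is described.

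A true size of 7% to 11% might be inferred from a correlation of 0.2 to 0.5 and two records per patient. That holds only if label or factor is constant within patient. With both correlations in that range, the figure is 5.5% to 8.0%.

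It is also fair that the encounter is a legitimate unit, that CHAID P values are exploratory split criteria, that ARM and CART as described use no significance test, and that system factors such as crowding are little affected. These points limit the consequence. Finally, query conditions are often left to a fuller plan, and the article says that several inclusion and exclusion criteria were applied. But the article states a rule for repeat patients, which a fuller plan would have to override.

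**Conclusion.** The point holds in a limited form. As written, the plan allows a case to be matched to the same patient's other visit and describes no allowance for several records from one patient. The first dilutes patient-level associations and can put an episode's error into a trigger-negative chart in Step 2. The second makes P values too small for patient-level factors in CHAID, and likewise in the Step 2 tests where one patient supplies several charts.

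Neither effect can be sized from the document. The test-size range given above rests on two records per patient and moderate correlations of both factor and label; it rises if either is constant within patient. Dilution is slight if self-pairs are few (OR 1.71 to 1.66 at 5%) and marked only if they are common. Self-matching remains a possibility that depends on the labelling of Trigger 1 and on how strictly provider and arrival time are matched.

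No confirmatory claim is at risk. The harm is to which patient factors are listed. It is worth correcting because the change is small and the article reports the data as still being cleaned.

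**What to change.** In Sampling for Control, replace the rule on repeat patients with three statements.

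1. Say which Trigger 1 encounter carries the positive label, and exclude the other visit of that episode from the control pool.
2. Never match a patient to themselves.
3. Use patient-clustered tests or patient-level resampling for the CHAID splits and the Step 2 comparisons. Keep all of a patient's records in the same fold of any validation. Repeat the analysis with one encounter per patient as a sensitivity analysis.

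The first two need a patient-identifier condition in the control query and a sentence each; the third needs a change in the analysis code. The cost is a small loss of eligible controls and slightly wider error bars.
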